#### Secondary outcomes

In order to confirm the impact of the OFA protocol on postoperative recovery, we will also measure the QoR-15 score at 48 h and 72 h after the surgery in all patients. We will evaluate the pain during effort (mobilization, cough or physiotherapy sessions) and the number of postoperative complications according to the POMS (postoperative morbidity survey) classification [27], assessed up to 72 h after the surgery. The postoperative consumption of morphine-equivalent will also be compared between the two groups. The lengths of stay in PACU and in the hospital will be measured.

We will compare the patient tolerance to the allocated protocol with the assessment of the hemodynamic status (intra-operative use of vasopressor or cessation of one of the drugs for hemodynamic purposes), heart-rhythm (< 35 or > 140 beats per minute for more than 30 s), and anaphylactic reactions. Another secondary outcome is the respect of the allocated protocol by the anesthesia team: OFA protocol will be considered complete if at least two of the following drugs are used between ketamine, lidocaine, clonidine, and magnesium sulfate, and if no intraoperative opioids are used; the standard group will be considered complete if lidocaine, clonidine, or magnesium sulfate are not used intra-operatively. The surgeon’s and anesthesiologist’s satisfactions concerning the anesthesia will be assessed after the surgery according to a numerical scale (rated from 0 to 10). We will also compare the patient satisfaction of anesthesia at 24 h via a numerated scale from 0 to 10 (0 = not satisfied and 10 = totally satisfied) and the presence or absence of intra-operative memorization.

Three months after surgery, a phone interview will be conducted to evaluate the chronic pain using the Brief Pain Inventory (BPI) [28] in its French short version, the quality of life using the French EQ-5D-3 L questionnaire (available on request on https://euroqol.org/), and the rate of neuropathic pain diagnosed using the DN-4 questionnaire [29].

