**Methods:**

The SOFA trial is a prospective, randomized, parallel, single-blind, monocentric study. Patients (*n* = 140) scheduled for major plastic, visceral, urologic, gynecologic, or ear, nose, and throat (ENT) surgeries will be allocated to one of the two groups. The study group (OFA group) will receive a combination of clonidine, magnesium sulfate, ketamine, and lidocaine. The control group will receive a standard anesthesia protocol based on opioid use. Both groups will receive others standard practices for general anesthesia and perioperative care. The primary outcome measure is the QoR-15 value assessed at 24 h after surgery. Postoperative data such as pain intensity, the incidence of postoperative complication, and opioid consumption will be recorded. We will also collect adverse events that may be related to the anesthetic protocol. Three months after surgery, the incidence of chronic pain and the quality of life will be evaluated by phone interview.

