### Intervention

The study aims to compare an OFA protocol to an anesthesia protocol based on standard practices. In both arms, patients will undergo general anesthesia, combined or not with local or regional anesthesia. The two protocols are detailed in Fig. 1.

None of the patients will receive premedication. Anesthetic monitoring will be the same in both groups, including pulse oximetry, electrocardiography, non-invasive blood pressure and/or invasive monitoring when indicated, body temperature, muscle relaxation (train-of-four stimulation), and bispectral index.

The OFA protocol (OFA group) begins before surgery with a clonidine infusion (under cardiac monitoring) at an initial rate of 50 μg/h, and then adapted according to hemodynamic stability (to keep systolic blood pressure in a range of ± 20% its basal value) with a maximal rate of 150 μg/h (100 μg/h for patients with body weight < 50 kg). Anesthesia will be induced and maintained with hypnotic drugs and curare left at the anesthesiologist’s discretion. No opioids should be infused. The clonidine infusion should be continued at the same infusion rate. The OFA protocol includes a magnesium sulfate infusion (40 mg/kg), a lidocaine infusion (1.5 mg/kg bolus dose in 10 min followed by 1.5 mg/kg/h continuous infusion), and a ketamine infusion (0.5 mg/kg bolus dose followed by a 0.2 mg/kg/h continuous infusion). The ketamine infusion should be stopped 30 min before the end of the surgery, and the lidocaine infusion will be stopped after 1 h in the postanesthesia care unit (PACU).

The standard anesthesia protocol associates hypnotic drugs, curare, and opioids (sufentanil or remifentanil) left at the discretion of the anesthetist in charge. A low-dose ketamine bolus (0.15 mg/kg) is allowed at anesthesia induction, possibly followed by repeated boluses since it is commonly used in our standard practice.

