## Discussion

Although OFA seems promising in the context of the opioid crisis, data are needed to objective its interest; our study will be powered to evaluate the impact of OFA on early QoR and give useful information on long-term benefit of reducing perioperative opioid use. In addition, we choose to use a combination of lidocaine, magnesium sulfate, ketamine, and clonidine to perform OFA. Other studies are underway which attempt to evaluate the quality of postoperative recovery using OFA, but either do not fully assess this “full” combination of drugs [33], or do not propose a continuous infusion throughout surgery [34]. In addition, we plan to evaluate OFA in a wide range of surgeries, while other studies focus on one type of surgical procedure only, in order to provide more generalizable results.

We choose to combine these different pharmacological classes during surgery for their different effects: analgesia, anti-hyperalgesia, anti-inflammatory effect, anti-nausea and anti-vomiting, and reduction of the neurohumoral stress response. In the anesthesia literature, different OFA protocols were described [35]. While OFA using dexmedetomidine has been reported to be effective during several types of surgery [13, 36], it may promote side effects, including increased risk of bradycardia and hypoxemia [9]. We thus prefer to incorporate clonidine as an alpha-2 agonist agent in our OFA protocol, because this molecule seems to be less responsible for severe bradycardia episodes [37] and seems to have longer positive effects [38].

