To evaluate OFA, we choose primary criteria focused on patients’ overall recovery. Indeed, in a recent international consensus, the SteP–COMPAC group has highlighted the value of postoperative recovery scales for standardizing outcomes in perioperative medicine [25]. The QoR-15 questionnaire appears reliable, sensitive, and easily achievable in clinical practice (2 to 3 min for the questionnaire to be fully completed). It gives information on postoperative recovery in a unidimensional approach, and the patient can complete the questionnaire alone or with the help of an assessor. Therefore, different studies have used this questionnaire to evaluate the impact of an intervention on patients’ perception of postoperative recovery [26]. Beyond assessing the quality of early recovery, we will also study the longer-term status (i.e., at 3 months). The study aims to investigate the pain profile of the patients, detect the presence of chronic pain, neuropathic pain, and estimate their quality of life. To our knowledge, our study would be the first to evaluate OFA on these long-term criteria.

In a nutshell, this study will compare an OFA protocol (based on a combination of four agents: clonidine, ketamine, magnesium sulfate, and lidocaine) versus a standard anesthesia protocol in patients scheduled for major non-orthopedic surgery, on their early QoR but also on their pain status and their quality of life at 3 months. The findings will also provide evidence of potential adverse events associated with this OFA protocol, helping to assess the benefit/risk ratio of the use of such a pharmacological combination.

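### The hemodynamic tolerance outcome merges vasopressor use with stopping a drug, although OFA has more protocol drugs to stop, and it counts vasopressors only during surgery although OFA lidocaine continues in the PACU

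*Protocol article*

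**What the plan says.** Under Secondary outcomes, the protocol article states: "We will compare the patient tolerance to the allocated protocol with the assessment of the hemodynamic status". Hemodynamic status is then specified as "intra-operative use of vasopressor or cessation of one of the drugs for hemodynamic purposes". Two further tolerance items follow: heart rates outside stated limits, and anaphylactic reactions. The text does not say which drugs count in which arm.

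The drugs differ by design. The abstract says: "The study group (OFA group) will receive a combination of clonidine, magnesium sulfate, ketamine, and lidocaine". Under Intervention, clonidine starts before surgery at an initial rate, "and then adapted according to hemodynamic stability (to keep systolic blood pressure in a range of ± 20% its basal value". On lidocaine, the same section says that "the lidocaine infusion will be stopped after 1 h in the postanesthesia care unit (PACU". Controls receive hypnotics, a muscle relaxant and sufentanil or remifentanil at the anesthetist's discretion, with low-dose ketamine boluses permitted. The adherence definition under Secondary outcomes confirms the contrast: "the standard group will be considered complete if lidocaine, clonidine, or magnesium sulfate are not used intra-operatively".

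Randomization and blinding states that the team giving the anesthetic knows the allocation.

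Other safety data are collected as well. The Safety section lists blood pressure and bradycardia episodes during anesthesia and surgery, adverse events possibly attributable to the protocol at later visits until discharge (censored at 30 days), and serious adverse events up to 3 months. Follow-up records the total dose of each perioperative medication and any complication in the PACU.

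**The concern.** The outcome joins two different things with an 'or'. Vasopressor use is a response that any patient in either arm can need. Stopping a drug is an action on the regimen, and the chance of it depends on what the regimen contains. OFA has three infused protocol drugs that controls should not receive, and one of them is already steered by blood pressure. Controls have discretionary drugs, with no fixed regimen against which a cessation can be recognised. An arm difference could then come from the hemodynamic response, from the number of drugs available to stop, or from how the unblinded team acts and records. The merged figure cannot separate these.

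The second issue is the window. Vasopressor use is counted intra-operatively only, but OFA exposure continues into the PACU through the lidocaine infusion. A vasopressor first needed there would not enter the comparison.

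At stake is whether this one tolerance comparison can be interpreted. The primary outcome is not affected.

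**Working it through.** **No stated figure for this outcome.** The article gives no rate, power or sample size for hemodynamic tolerance. Its only computed design figure is for the primary outcome, and it reproduces. With a difference of 8, SD 16, two-sided 0.05 and power 0.80, the normal formula gives 63 per arm, or 126 in total; 126 / 0.90 = 140. From this I take 140 / 2 = 70 patients per arm.

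**Inputs assumed.** v is the vasopressor rate, equal in both arms (0.30, 0.50, 0.70). s is the share of the remaining patients in whom a drug is stopped for hemodynamic reasons, s1 in OFA and s0 in control.

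**Formula.** The merged rate in an arm is v + (1 − v)s. The arm difference is (1 − v)(s1 − s0).

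Example with v = 0.30, s1 = 0.10, s0 = 0: OFA 0.30 + 0.70 × 0.10 = 0.37; control 0.30; difference 7.0 points.

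| s1 | s0 | v = 0.30 | v = 0.50 | v = 0.70 |
|---|---|---|---|---|
| 0.05 | 0 | +3.5 | +2.5 | +1.5 |
| 0.10 | 0 | +7.0 | +5.0 | +3.0 |
| 0.20 | 0 | +14.0 | +10.0 | +6.0 |
| 0.20 | 0.10 | +7.0 | +5.0 | +3.0 |
| 0.20 | 0.20 | 0 | 0 | 0 |

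Differences are in percentage points, OFA minus control. Vasopressor use compared alone differs by 0 in every cell.

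**Chance of a significant result.** Take a plain two-sided 5% comparison of proportions, normal approximation with unpooled standard error and 70 per arm. For v = 0.30, s1 = 0.10, s0 = 0:

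- SE = √(0.37 × 0.63/70 + 0.30 × 0.70/70) = 0.0796
- z = 0.07/0.0796 = 0.88
- rejection probability = Φ(0.88 − 1.96) + Φ(−0.88 − 1.96) ≈ 14%

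With s0 = 0 and s1 = 0.05, 0.10 and 0.20, the results are:

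- v = 0.30: about 7%, 14% and 41%
- v = 0.50: about 6%, 9% and 22%
- v = 0.70: about 5%, 7% and 13%

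The article states no test for this outcome, so these figures only give a sense of scale.

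**Window.** Suppose that, among patients without an intra-operative event, a first vasopressor is needed in the PACU in 10% of OFA and 5% of control patients. The uncounted difference is (1 − v)(0.10 − 0.05): 3.5, 2.5 and 1.5 points for v = 0.30, 0.50 and 0.70. On these assumptions, OFA events are undercounted, which works against the inflation in the table.

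**The case against.** The case against has real force on several points.

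- **Controls also have drugs to stop.** Opioids, hypnotics and optional ketamine can all be withheld for low pressure, and the text does not restrict the drugs to those of OFA. A reader might infer that cessation is practically an OFA-only event, but the documents do not say so. The asymmetry is one of degree and depends on how the undefined phrase is read. That ambiguity is itself part of the problem.
- **Cessation is a legitimate sign of intolerance.** The outcome is tolerance of the allocated protocol, and having to stop a drug for hemodynamic reasons is a failure of tolerance. Stopping a drug may also replace a vasopressor, so dropping cessation could hide OFA intolerance. This stands, and cessation should stay as a measure. Nor does a rate adjustment alone count, since the outcome refers to cessation.
- **The window is not uniformly closed.** The intra-operative limit clearly applies to vasopressor use, its reach over cessation is unclear, and the heart-rate criterion has no such limit. It cannot be said that all postoperative hemodynamic events are left out.
- **Clonidine carry-over is not documented.** The Discussion says clonidine "and seems to have longer positive effects [38", which concerns benefits in contrast with dexmedetomidine. It does not support prolonged hypotension. The window point rests on the lidocaine timing alone.
- **Benefit/risk does not depend on this outcome.** A reader might infer that the trial's benefit/risk assessment is distorted. The Discussion bases it on adverse events in general ("The findings will also provide evidence of potential adverse events associated with this OFA protocol, helping to assess the benefit/risk ratio"), and those are collected separately. The inference is not supported.

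What remains is the merged definition, the unnamed drugs, the unblinded decision on both components, and the vasopressor window that ends with surgery.

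**Conclusion.** The point holds for one secondary safety outcome. As worded, a difference in hemodynamic tolerance can partly reflect how many stoppable drugs each arm has, and it omits vasopressor use in the PACU while an OFA infusion is still running.

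The size cannot be taken from the documents. On the assumed rates, with stopping in 10% to 20% of the remaining OFA patients and in no controls, the merged outcome differs by 3 to 14 points although vasopressor use is equal. The zero rate in controls is the most influential assumption: the difference shrinks when control cessations are counted and vanishes when they are equally frequent. Nor does equal vasopressor use prove equal hemodynamics, because stopping a drug may have avoided a vasopressor. The table therefore shows what merging does to the comparison. It does not show a false-positive rate.

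The merged definition may raise the OFA count and the short window may lower it. The net direction is unknown, and nothing shows that the two cancel.

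**What to change.** 1. Make vasopressor use an outcome of its own (yes/no and total dose), compared between arms from the start of the allocated protocol to PACU discharge.
2. Report drug cessation for hemodynamic reasons separately by arm, keep it as a tolerance measure, and name the drugs that count in each arm.
3. Show both beside the hypotension and bradycardia episodes already collected under Safety, so that the reader can see whether stopping drugs replaced vasopressors.

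The cost is a rewording of one secondary outcome and a few more eCRF entries for vasopressors in the PACU. Total doses of perioperative medications are already recorded under Follow-up. For the PACU, the article names doses of pain medications only. Treatment and sample size do not change. Separate reporting gives up the single summary figure, and cessation will still reflect decisions of an unblinded team, which should be said when it is reported.

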In both arms, according to recent recommendations, anesthesiologists are prompted to infuse an antimicrobial prophylaxis [17], to apply a protective ventilation strategy (tidal volume between 6 and 8 ml/kg, respiratory rate for an end-tidal CO_2_ value at 35–40 mmHg, a positive end expiratory pressure) [18], and to treat perioperative hypotension and hypovolemia [19]. The depth of anesthesia is monitored by a bispectral index sensor (target 40–60). Postoperative pain, nausea, and vomiting are managed according to the unit protocols. The use of local or regional anesthesia is allowed in both groups (in the OFA group, the protocol stipulates not to use opioids as adjuvant). In the PACU, if the patient experiences acute pain (defined as a pain analog scale ≥ 4), morphine or oxycodone titration will be started (bolus of 1 to 2 mg, with a 5-min delay between two doses) until pain relief is achieved. The analgesic management will be continued in the ward using IV PCA and/or oral opioids. The doses of opioids (i.e., morphine and oxycodone) will be converted into morphine-equivalent doses according to the following rule: 1 mg oral morphine = 1/2 mg oral oxycodone = 1/3 mg IV morphine; 1 mg IV morphine = 1 mg IV oxycodone. Patients will be discharged to the ward when their modified Aldrete score is ≥ 12 [20].

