### Statistical analysis

All analyses will be performed with R software (version 3.6.3). The main analysis will be in intention-to-treat and will include all randomized patients. Patients will be analyzed according to their randomization group. A per-protocol analysis will be performed as a sensitivity analysis to assess the main analysis robustness. A flow chart of all patients (Fig. 3) and descriptive statistics will be used to describe baseline characteristics. Data will be presented by their mean with standard deviation, median with interquartile range, number with the percentage of sample (%), or 95% confidence interval, according to their normal or non-normal distribution. We will report both absolute and relative measures for the comparisons between endpoints.

For the primary endpoint, we will use multivariate imputation for chained equations (with five imputations) via the mice package in R and perform a pooled-linear regression model, allowing us to perform an intention-to-treat analysis even if missing data. The covariates included in this analysis will be the allocation group, the type, and the surgery severity. This statistical method will also be used to analyze the QoR-15 at 48 and 72 h as secondary endpoints. To eliminate any influence of the phone evaluation, we will perform a sensitivity analysis just on the QoR-15 surveys collected in the ward.

We will also impute data for the analyses of other secondary endpoints: the rate of chronic pain patients at three months identified by the BPI via a logistic regression (same adjustment covariates) as well as for EQ-5D visual analog score via a linear regression (same adjustment covariates). The other endpoints will not be analyzed with the multiple imputation method. We reserve imputation for the endpoints included in the hierarchical scheme of the type I error management.

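### The standard-arm completeness rule does not require the opioid that defines that arm and gives no route for lidocaine, so protocol adherence can be misclassified in either direction.

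*Protocol article*

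**What the plan says.** In the protocol article, the Methods paragraph of the abstract describes the comparator: "The control group will receive a standard anesthesia protocol based on opioid use". The Intervention section repeats this in detail: "The standard anesthesia protocol associates hypnotic drugs, curare, and opioids (sufentanil or remifentanil) left at the discretion of the anesthetist in charge". Controls may also receive low-dose ketamine boluses. On blocks, the same section says: "The use of local or regional anesthesia is allowed in both groups".

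The Secondary outcomes section lists adherence by the anesthesia team as an outcome and gives one rule per arm:

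- OFA arm: "OFA protocol will be considered complete if at least two of the following drugs are used between ketamine, lidocaine, clonidine, and magnesium sulfate". A second condition rules out any opioid during the operation.
- Standard arm: "the standard group will be considered complete if lidocaine, clonidine, or magnesium sulfate are not used intra-operatively".

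The Statistical analysis section makes the main analysis intention-to-treat in all randomized patients and adds: "A per-protocol analysis will be performed as a sensitivity analysis to assess the main analysis robustness". It does not say which patients form the per-protocol population.

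**The concern.** The two rules are not built alike. The OFA rule has a condition on opioids, the feature that separates the arms. The standard rule has none; it lists only drugs that must be absent. A control managed with general anesthesia, a regional block and ketamine, without any intra-operative opioid, is therefore recorded as having received the standard protocol.

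Two wording problems add to this. Lidocaine is named without a route, although it can be used for a block that both arms may receive. And a list of three drugs joined by 'or' before a negative can be taken to mean that the absence of any one of them is enough.

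The direct stake is the adherence outcome, whose figure for the standard arm may be too high or too low. The conditional stake is the per-protocol analysis. If its population follows these rules, OFA patients who received an opioid leave the set, while controls never leave for lacking one.

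**Working it through.** **1. Enumerate the rules.** Take five yes/no items: ketamine, lidocaine, clonidine, magnesium sulfate, intra-operative opioid. There are 2^5 = 32 patterns.

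*Standard rule read as 'none of the three used'.* Lidocaine, clonidine and magnesium are fixed at no; ketamine and opioid are free, so 2 × 2 = 4 patterns are complete:

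| Ketamine | Opioid | Standard-complete under the rule | Fits the arm definition |
|---|---|---|---|
| no | yes | yes | yes |
| yes | yes | yes | yes |
| no | no | yes | no |
| yes | no | yes | no |

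Two of the four contain no opioid. This counts patterns, not patients.

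*OFA rule.* No opioid and at least two of four drugs: C(4,2) + C(4,3) + C(4,4) = 6 + 4 + 1 = 11 patterns. Only one of the two or more drugs can be ketamine, so each pattern has at least one of lidocaine, clonidine or magnesium. The overlap with the four standard-complete patterns is 0.

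*Standard rule read as 'not all three used'.* Of the 8 patterns of lidocaine, clonidine and magnesium, 7 qualify; 7 × 2 × 2 = 28 patterns are standard-complete. Of the 11 OFA-complete patterns, only the 2 containing all three drugs (with or without ketamine) fall outside, so 11 − 2 = 9 are complete under both rules.

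**2. Lidocaine route.** A control who received an opioid and lidocaine for a permitted block, but no clonidine or magnesium, has followed the Intervention section, yet fails the rule. In the OFA arm the same gap works the other way: ketamine plus block lidocaine, without an opioid, would reach the two-drug threshold using only drugs that controls may also receive.

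**3. Net effect on reported adherence.** Let *a* be the share of controls with no opioid and none of the three listed drugs, and *b* the share with an opioid whose only listed drug was block lidocaine. Then

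reported adherence − adherence to the arm as defined = *a* − *b*.

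The article gives neither share, so the sign is unknown.

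**4. Possible size in a per-protocol analysis.** Inputs from the Sample size section: difference 8.0, SD 16, two-sided alpha 0.05, power 0.8.

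- Plan's figure: n per arm = 2 × (1.960 + 0.842)² × 16² / 8² = 62.8, rounded up to 63; total 126; 126 / 0.9 = 140. The stated figures reproduce.
- Standard error at 63 per arm: 16 × √(2/63) = 2.85. Power at 8 points: Φ(8/2.85 − 1.96) = 0.80.
- Assumption: a share *f* of standard-complete patients had no opioid and recovered like OFA patients. The contrast is then 8 × (1 − *f*).

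| *f* (assumed) | Contrast | Power at 63 per arm |
|---|---|---|
| 0% | 8.0 | 0.80 |
| 5% | 7.6 | 0.76 |
| 10% | 7.2 | 0.71 |
| 20% | 6.4 | 0.61 |

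The reference row is a trial with full adherence, not the intention-to-treat result. The same patients are in the intention-to-treat set, so the rule does not push the per-protocol estimate below it. It fails to remove a dilution that the per-protocol analysis is meant to remove. The power column is for scale only; the sensitivity analysis was not powered separately.

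**The case against.** A reader might infer that the per-protocol check does not compare the two protocols at all. The documents do not support that. The OFA rule excludes any intra-operative opioid, and on the ordinary reading, with lidocaine taken as the study infusion, no drug pattern is complete under both rules. The contrast can be diluted; it is not lost.

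A reader might also infer that the two-of-four threshold is a defect, because the trial is presented as a four-drug combination and ketamine is allowed in controls. This does not stand either. The threshold is a pragmatic choice in a trial that expects a drug may be stopped for hemodynamic reasons, and ketamine alone cannot meet it. A stricter drug count would redefine the intervention and select patients on tolerance after randomization.

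Other points on that side are fair. The link between the completeness rule and the per-protocol set is an inference; the full protocol or the analysis plan may define that set. Adherence is not among the imputed endpoints that the article identifies with the hierarchical testing scheme. Opioid-free controls may be uncommon, since all patients have general anesthesia for surgery of at least 90 min that usually calls for IV morphine PCA. 'None used' is the natural reading of the list, and the Intervention section describes study lidocaine as an infusion.

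These points limit the consequences. They do not repair a stated rule that leaves out the feature by which the same article defines the arm, nor do they supply a route for lidocaine.

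**Conclusion.** The point holds for the standard-arm rule. As written, it counts controls who received no opioid as complete and counts some controls who followed the Intervention section as incomplete. Reported adherence in that arm can be wrong in either direction, by an amount that the article does not allow one to estimate.

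Any effect on the per-protocol analysis is conditional on two assumptions: that this rule sets its population, and that opioid-free controls recover like OFA patients. The 7.6 to 6.4 points for assumed shares of 5% to 20% then show the scale of dilution left in place, measured against full adherence. They are not a forecast, and they are not a loss relative to intention-to-treat. The primary analysis is untouched, and the OFA threshold can stay. This should be corrected, but it does not threaten the trial's main conclusion.

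**What to change.** Reconcile the rule in Secondary outcomes with the abstract and the Intervention section:

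- Classify a standard patient as complete only if at least one intra-operative opioid was given **and** none of systemic lidocaine, clonidine or magnesium sulfate was given.
- State that lidocaine used for a permitted local or regional block counts in neither arm's rule.
- Write 'none of' in place of the ambiguous 'or'.
- State in Statistical analysis whether these rules define the per-protocol population; if they do not, say what does.

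This is a classification for analysis and changes no patient's treatment. The cost is mainly wording: the Follow-up section already records the total dose of each medication. The lidocaine route must also be on record and would have to be added if it is not. The per-protocol set, if built on this rule, will differ slightly and may be smaller.
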